### Cost data

Data is collected for each individual patient in the project. The hospital costs will be based on the initial emergency room visits, the hospital stay in the orthopaedic surgical ward or intensive care units, readmissions and outpatient visits in the 12 months follow-up period. The costs related to the Scand-Ankle trial, including the project visits for outpatients, will be categorised as either GSP-A-related costs (staff salaries) or extra project costs (such as extra laboratory tests, medications and transportation). The costs related to primary care and other health care sectors will be derived from the consultation fees for general practitioners and “doctors on call”, average wages for specialists, home helpers, day care nurses, etc.

### Intervention

Patients allocated to the intervention group receive the GSP-A aiming at alcohol abstinence before, during and 6 weeks after surgery. The intervention will be initiated after the baseline interview has been completed and is conducted by research staff. To qualify for the intervention research personnel has to take part in a 2-day educational programme followed by practical training. The GSP-A consists of weekly intervention meetings at the orthopaedic ward or outpatient clinic (5 in total); see Table 1.

**Table 1 Tab1:** **Gold standard programme for alcohol cessation intervention**

**Patient education programme**	
1.	First meeting (during admission): Level of motivation, ambivalence, pros and cons
2.	Second meeting (after 1 week): Dependence, withdrawal symptoms (experiences and expectations)
3.	Third meeting (after 2 weeks): Relapse (description and management)
4.	Fourth meeting (after 3 weeks): Benefits by short and long term alcohol abstinence
5.	Fifth meeting (after 4 weeks): Continued alcohol abstinence or reduced intake following intervention
**At each meeting**	
• Thiamine and B-vitamins (300 mg × 7 weekly)	
• Alcohol withdrawal prophylaxis and treatment (chlordiazepoxid 10 mg)	
• DIS support (200 mg × 2 weekly) supervised at weekly meetings (not administrated if patients test positive on an alcohol breath test)	
• Alcohol biomarkers (blood, urine and breath tests)	
• ECG	

The study medication is provided for free and transportation for the weekly meetings will be reimbursed. Patients can also contact the research personnel via phone or e-mail.

The structured patient education programme covers different topic at each meeting. At the first meeting, the patients will receive further information on the association between alcohol intake and postoperative complications. They will also be tested for ambivalence and level of motivation using different motivation scales to support patients’ empowerment: the LINE (see Table 2), the BOX (see Table 3) and the CIRCLE (see Figure 2) [39,40].

**Table 2 Tab2:** **The LINE for identification**

**Information**	- All operations can cause complications, but many complications can be prevented. An important part of the prevention is your own effort as well as the support from the hospital.
	Question 1:
	- How important is it for you to prevent complications in relation to your surgery – on a scale from 0 to 10?
**Information**	- Hazardous drinking patients have 3 to 4 times more complications than others.
	Question 2:
	- How important is it for you to stop drinking alcohol in relation to your operation – on a scale from 0 to 10?

**Table 3 Tab3:** **The BOX for assessingambivalence**

**What are the advantages of keep drinking alcohol?**	**What are the disadvantages of keep drinking alcohol?**
What are the disadvantages of giving up alcohol?	What are the advantages of giving up alcohol?

**Figure 2 Fig2:**
[figure not shown]
The stages of change model.

The education topic at the second meeting focuses on dependence and withdrawal symptoms with a particular focus on experiences and conceptions. The patients may develop stress caused by abstinence from alcohol. The withdrawal stress response is reduced by offering supportive medical treatment against development of mild to moderate withdrawal symptoms (minor doses of chlordiazepoxide), while severe alcohol withdrawal symptoms are treated in accordance with the recommendations and clinical guidelines from the psychiatric department related to the hospital. The personal stress is expected to be reduced by the empathic and empowering intervention. At the third meeting the focus is on relapse management and situations, where it is most likely that the patients will feel like drinking again. In case of relapse, the aim is to focus on the experiences the patients have gained while being abstinent and use these to initiate a new change and support the patients to resume abstinence. The patients are encouraged to participate in all meetings whether they comply with intervention or not. At the fourth meeting other benefits of short- and long-term alcohol abstinence is discussed with the patients, and at the last meeting the patients are encouraged to either continued alcohol abstinence after the 6-week intervention period (especially for patients who have experienced withdrawal symptoms), or if they do not want to be abstinent to keep their intake at a non-hazardous level. Following the intervention the patients can be referred to outpatient alcohol treatment facilities on their request.

### Control

Patients allocated to the control group receive standard care for patients with hazardous alcohol intake undergoing ankle fracture surgery including surveillance/scoring for alcohol withdrawal symptoms and related treatment according to the clinical guidelines in the wards. The standard procedures regarding alcohol are often non-interventional and characterised by short information and advices about changing alcohol habits. All control patients are informed about the possibility for alcohol intervention in their neighbourhood by delivery of a folder.

### All patients

Both groups receive routine procedures regarding general patient information, thromboembolic prophylaxis and antibiotics, anaesthesia, surgical intervention and other procedures according to the clinical guidelines for the operation at the involved wards. All patients have benzodiazepines for pre-medication. Sufficient thiamine is administered prior to eventual infusion of glucose.

In case of incidental findings all necessary steps would be taken for related information, diagnosing, intervention and follow-up. Severely dependent patients, including previous alcohol withdrawal symptoms, are not included in the study, but are referred to conventional treatment and observation according to national and international clinical guidelines.

### Measures

The primary and secondary outcomes will be evaluated at follow-up points after 6 weeks, 3, 6, 9 and 12 months.

#### Primary outcomes

Postoperative minor and major complications requiring treatment: Wound complications, dislocated fracture, mal-union and secondary surgery and others such as pneumonia, thrombosis and neurological complications. Postoperative complications will be evaluated by an orthopaedic specialist blinded to patients’ group allocation.Continuous alcohol abstinence and non-hazardous drinking validated biochemicallyCost-effectiveness

#### Secondary outcomes

The secondary outcomes include length of stay, reconvalescense (time until returning to work), self-evaluated health (SF36), degree of alcohol withdrawal symptoms and cost-effectiveness regarding changes in health-related quality of life (QALY [41]).

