### Recruitment process and inclusion criteria

All ankle fracture patients admitted to the orthopaedic wards and scheduled for surgery are screened for eligibility by the research staff, and patients fulfilling the inclusion, but not the exclusion criteria, are invited to participate in the trial. The inclusion criteria are traumatic ankle fracture requiring internal fixation (osteosynthesis), informed consent, and randomisation within 36 hours after entering the orthopaedic ward. The fracture can be open or closed as well as simple or comminuted. The exclusion criteria are major trauma involving other fractures or major lesions, preoperative severe psychiatric disorders (including drug addiction, severe alcohol dependence [defined as experience of delirium or seizures during abstinence from alcohol] and dementia) or other conditions of reduced ability for giving informed consent; pathological fractures, pregnancy and lactation; allergy to benzodiazepines or DIS; uncompensated chronic diseases (including fulminant cardiac or liver insufficiency, which are contraindications for DIS) or ASA score 4-5 [31]; cancelled operation and withdrawal of informed consent.

Patients are included after informed consent, which can be obtained before or after the operation but within the 36 hours after admission. The patients can withdraw the informed consent at any time without any explanation and without consequences for their treatment or contact to the staff. For patients not giving or withdrawing their informed consent research staff will ask permission for follow-up via their medical recording solely for the purpose of the project.

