### Data collection

Baseline data will be collected for all included patients during admission in interviews: A detailed alcohol profile on intake over time (Timeline Follow-back [32]), ICD-10 criteria for alcohol dependency [33], test for alcohol use disorders (AUDIT-C [34]), alcohol withdrawal symptoms (CIWA-Ar [35]), breath test (ethanol during expiration), blood sampling for liver function (haemoglobin, alkaline phosphates, gamma-glyteryl-transferase, amino-transferases, bilirubine) and for alcohol markers (carbohydrate-deficient transferring, ethanol, phosphatidylethanol, mean cell volume, serum, EDTA–plasma and citrate-plasma); urine sampling for alcohol markers (ethyl glucuronide, ethyl sulphate, ethanol).

Furthermore, baseline characteristics regarding age and sex, socio-demographic factors, other lifestyle factors (smoking, overweight, risk of malnutrition and physical inactivity [36]), co-morbidity, self-rated ankle function, and self-evaluated health assessed in the SF-36 questionnaire [37] will be obtained for all patients.

During admission the following information will be collected from the medical records: AO-classification of the ankle fracture and surgical characteristics; ASA-score [31], operative procedure, antibiotics and thrombo-embolic prophylaxis, type of anaesthesia, blood loss, infusions, implants and surgical or anaesthetic problems. Besides, length of hospital stay, use of resources and medicines, discharge or transfer will be registered for all patients.

Follow-up visits will be conducted after 6 weeks, 3, 6, 9 and 12 months in the orthopaedic outpatient clinics. Patients will be evaluated on postoperative complications and second surgery, Olerud-Molander Ankle Score [38], dorsal plantar flexibility (after 3, 6, 9 and 12 months) and fracture status after 12 months confirmed by x-ray (satisfactory healing, secondary dislocation or non-union. Effect on alcohol intake will be assessed by Timeline Follow-back [32], alcohol withdrawal symptoms (CIWA-Ar [35]), breath test (ethanol during expiration) as well as blood sampling for liver function, alcohol markers and urine sampling for alcohol markers. Besides data on rehabilitation, readmissions, ED, general practitioners, specialist doctor, physiotherapist and occupational therapist, alcohol treatment services, nursing home, community nurse, home care, return to work and/or previous activity level, and use of medicines will be collected at all follow-up points.

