### Sample size

Sample size calculations are restricted by this being the first study evaluating the effect of alcohol cessation intervention in acute fracture surgery, and the number of patients needed differ depending on the outcome.

The effect on alcohol abstinence is based on the preoperative intensive alcohol interventions, which showed a very high effect above 90% in the intervention groups versus less than 10% in the control groups [16]. However, a more moderate effect is expected in acute fracture surgery with 50% abstainers in the GSP-A group after 6 weeks. This corresponds to a minimum of 2×12 patients.

Postoperative complication rates among ankle fracture patients were 30% for patients drinking at least 5 drinks per day versus 10% in patients without hazardous alcohol intake in a case-control study [42]. If similar complication rates after 6 weeks are expected in the control and GSP-A group respectively, a total maximum of 2×59 patients should be recruited over the 3 to 4 years inclusion period.

The number of patients for the cost-effectiveness analyses is based on the expected effect on the clinical outcomes [43].

All sample size calculations are based on a power of 80% and a risk of type 1 failure on 5%. Also to reduce differences between patient populations, each centre should include about 20 patients.

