### Statistical analyses

The analyses will be performed blinded. The groups are compared regarding primary and secondary outcomes using Chi-square/Fisher’s exact test for frequencies and Mann-Whitney test for continuous outcomes. Analyses will be conducted using intention-to-treat principles. A p-value < 0.05 is considered statistically significant. Subgroup analyses for determination of prognostic factors are done through logistic regression analyses.

The cost-effectiveness of the GSP-A will be estimated by comparing the incremental cost to the incremental effect of the two groups. The GSP-A is considered more cost-effective than standard care if it is less costly and more effective. If the GSP-A is more costly and more effective, the additional cost per abstainer has to be considered worth paying [44].

Data will be analysed using IBM SPSS v. 19 and Excel 2010.

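### Time until returning to work is censored, but the only test the plan gives for it is Mann-Whitney, with no rule for patients who have not returned or are lost; the cost runs from small to large depending on that rule

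*Protocol article*

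**What the plan says.** Under Secondary outcomes, the protocol article lists "reconvalescense (time until returning to work" among several others. Under Measures it fixes when outcomes are assessed: "The primary and secondary outcomes will be evaluated at follow-up points after 6 weeks, 3, 6, 9 and 12 months". Data collection confirms the source of the information: "return to work and/or previous activity level, and use of medicines will be collected at all follow-up points". Follow-up for this outcome therefore ends at 12 months. It can end earlier, because the recruitment section says: "The patients can withdraw the informed consent at any time without any explanation".

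For the comparison of groups on primary and secondary outcomes, Statistical analyses gives one rule: "Chi-square/Fisher’s exact test for frequencies and Mann-Whitney test for continuous outcomes". It adds: "Analyses will be conducted using intention-to-treat principles". The only other methods named are logistic regression for prognostic subgroup work and an incremental cost-effectiveness comparison. No Kaplan-Meier, log-rank or Cox method appears. The article does not put Mann-Whitney and return to work side by side; the link follows from the general rule, because a time is not a frequency.

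**The concern.** A patient still off work at 12 months has no return time, only the knowledge that it exceeds 12 months. A patient who withdraws at, say, 4 months has one that exceeds 4 months. Mann-Whitney has no place for this kind of information. The analyst must leave such patients out, or give them a value by a rule that the article does not state.

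The choice matters most if the programme works by getting more patients back to work. Those who have not returned then carry much of the difference, and a comparison confined to returners leaves them out. The Perspectives section expects fewer sick days and savings to society, and this outcome bears directly on that expectation.

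**Working it through.** **Inputs from the article.** 59 per group (Sample size), 1:1 allocation, last visit at 12 months, 5% significance level (two-sided assumed).

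**Assumed, because the article gives no figure.** Share back at work by 52 weeks: 70% control, 90% intervention. Exponential times, hence proportional hazards. Loss of 0% or 20%. All 59 per group in work before the fracture.

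**1. The plan's own figure.** For complications, 30% v 10%, 80% power, two-sided 5%, unpooled variance: (1.960 + 0.842)² × (0.3×0.7 + 0.1×0.9) / 0.2² = 58.9, so 59. This reproduces the 2×59. It rests on complications; the article gives no calculation for return to work.

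**2. The scenario.** Hazards per week are −ln(0.30)/52 = 0.0232 and −ln(0.10)/52 = 0.0443. The hazard ratio is 1.91, with logarithm 0.648. With complete follow-up, the chance that an intervention patient returns before a control patient is 1.91/2.91 = 0.657, a rank effect of 0.657 − 0.5 = 0.157.

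**3. Log-rank, no loss.** Expected returns: 59×0.7 + 59×0.9 = 94.4. z = 0.648 × √(94.4/4) = 3.15. Power = Φ(3.15 − 1.96) = 88%.

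**4. Mann-Whitney, non-returners ranked last, no loss.** The chance that neither member of a pair returns is 0.3×0.1 = 0.03. Rank effect: 0.657×0.97 + 0.5×0.03 − 0.5 = 0.152, which is 97% of 0.157. Standard error, with 20% of patients tied: √[119/(12×59×59) × (1 − 0.2³)] = 0.053. z = 2.86, power = Φ(0.90) = 82%.

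**5. Mann-Whitney, returners only, no loss.** Expected numbers are 41.3 and 53.1. The chance that the intervention patient is earlier, given that both return, is (0.7 − 0.343×0.97)/(0.7×0.9) = 0.582, a rank effect of 0.082, or 53% of 0.157. Standard error: √[95.4/(12×41.3×53.1)] = 0.060. z = 1.37, power = Φ(−0.59) = 28%.

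**6. Simulation of the same scenario.** It agrees with steps 3 to 5 and adds loss to follow-up.

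| Handling | 59 per group, no loss | 59 per group, 20% loss | 40 per group, 20% loss |
|---|---|---|---|
| Mann-Whitney, returners only | 27% | 23% | 16% |
| Mann-Whitney, censored time taken as observed | 82% | 73% | 56% |
| Mann-Whitney, no return date set to 52 weeks | 82% | 78% | 59% |
| Log-rank | 88% | 86% | 69% |

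Without loss, the second and third rows are the same analysis. The last column shows what happens if fewer patients were in work.

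**7. Range over the assumed return rate.** Simulated power with hazard ratio 1.75, 59 per group, no loss:

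| Control patients back by 12 months | Returners only | Non-returners at 12 months | Log-rank |
|---|---|---|---|
| 50% | 8% | 63% | 66% |
| 70% | 18% | 72% | 79% |
| 80% | 32% | 73% | 83% |
| 90% | 49% | 72% | 81% |
| 95% | 61% | 75% | 85% |

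The returners-only test keeps 32% of the rank effect at 50% return, 50% at 70% and 88% at 95%. Setting non-returners to 12 months keeps 85% at 50% return, 96% at 70% and about 100% from 80% upwards.

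If the programme changes only whether patients return and not when, the returners-only test has about 5% power, its own significance level. At 70% control return without loss, setting non-returners to 12 months then gives 42%, against 58% for log-rank.

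With no true effect, all methods rejected in about 4–6% of runs. In these scenarios the issue is therefore power, not false positives.

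**The case against.** The strongest reply is that a rank test needs only an ordering. With a common 12-month horizon, everyone not back by then belongs behind everyone who is, so Mann-Whitney can include all patients who complete follow-up. In the scenario above this costs about 6 points of power (82% v 88%). That stands.

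A reader might infer that the plan throws away most of any effect on return to work. The documents do not support that. It would require that patients without a return date are dropped, which the article nowhere says and which its intention-to-treat sentence argues against. Even then, the loss is half or more only if about 30% or more of controls are still off work at 12 months, or if the effect lies mainly in whether patients return.

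It can also be said that an article condenses, and that rules for non-returners belong in a fuller document. For the detailed rules this is fair. But the article does name a test for every primary and secondary outcome, and for this one that test does not account for censoring. Ranking last also does not solve loss before 12 months, where the patient's true position is unknown.

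**Conclusion.** The point holds in a limited form. Return to work is censored at 12 months or at earlier loss, the plan's general rule sends it to a test that does not account for this, and no rule for non-returners or losses is stated. The cost runs from modest (82% v 88% with non-returners ranked last) to severe (27% v 88% with returners only). With 20% loss the range is 23% to 78%, against 86% for log-rank. Log-rank had the highest power under every handling tried, and its advantage over including all patients in Mann-Whitney grew when patients were lost early.

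These figures rest on assumed return rates, effect size and loss, since the documents give none. Fewer than 59 per group are likely to have been in work, so the powers are optimistic for every method. The outcome is secondary: neither the primary outcomes nor the 2×59 is touched.

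**What to change.** Restrict the analysis to patients in work before the fracture. Analyse time from surgery to return to work by Kaplan-Meier curves with a log-rank test stratified by centre, in line with the stratified randomisation, or by a Cox model. Censor at last contact or at 12 months, and state this in the plan. If only the visit interval of the return is known, say so and use a method for interval-censored times.

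The cost is a few lines of wording and slightly more analysis work; the methods are standard in general statistical software. No new data, visits or patients are needed, and since the analyses are to be done blinded, the change can be fixed before the groups are revealed. Log-rank and Cox assume that loss to follow-up is unrelated to the chance of returning, so losses should be reported by group.

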### Sample size

Sample size calculations are restricted by this being the first study evaluating the effect of alcohol cessation intervention in acute fracture surgery, and the number of patients needed differ depending on the outcome.

The effect on alcohol abstinence is based on the preoperative intensive alcohol interventions, which showed a very high effect above 90% in the intervention groups versus less than 10% in the control groups [16]. However, a more moderate effect is expected in acute fracture surgery with 50% abstainers in the GSP-A group after 6 weeks. This corresponds to a minimum of 2×12 patients.

Postoperative complication rates among ankle fracture patients were 30% for patients drinking at least 5 drinks per day versus 10% in patients without hazardous alcohol intake in a case-control study [42]. If similar complication rates after 6 weeks are expected in the control and GSP-A group respectively, a total maximum of 2×59 patients should be recruited over the 3 to 4 years inclusion period.

The number of patients for the cost-effectiveness analyses is based on the expected effect on the clinical outcomes [43].

All sample size calculations are based on a power of 80% and a risk of type 1 failure on 5%. Also to reduce differences between patient populations, each centre should include about 20 patients.

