### Randomisation, allocation concealment and sequence generation

A computer-generated list of random numbers will be used for allocation of the patients. The randomisation sequence is created using www.sealedenvelope.com statistical software, and is stratified by centre with a 1:1 allocation using random block sizes. The list is generated by a researcher not otherwise involved in the project and prior to the commencement of recruitment. The allocation sequence will be concealed from the research staff enrolling and assessing participants in sequentially numbered, opaque, sealed and stapled envelops that are impermeable to intense light. Corresponding envelops will be opened only after the patients have given informed consent and it is time to allocate the intervention group.

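### The recruitment maximum of 2×59 equals the number needed with a 6-week complication outcome, so the stated 80% power holds only if essentially no randomised patient lacks that outcome

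*Protocol article*

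**What the plan says.** The Sample size section takes its complication rates from a case-control study in ankle fracture patients: "30% for patients drinking at least 5 drinks per day versus 10% in patients without hazardous alcohol intake". It carries these over to the two arms at one time point: "If similar complication rates after 6 weeks are expected in the control and GSP-A group respectively". From this it concludes that "a total maximum of 2×59 patients should be recruited over the 3 to 4 years inclusion period". The error rates are common to all its calculations: "All sample size calculations are based on a power of 80% and a risk of type 1 failure on 5"%. The section mentions no allowance for patients without an outcome.

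The section on recruitment and inclusion criteria ends its exclusion list with "cancelled operation and withdrawal of informed consent". It also says that consent may be given before or after the operation and may be withdrawn at any time, and that patients who refuse or withdraw will be asked whether their medical records may be followed. The randomisation section says that the envelope is opened only once consent has been given. The Statistical analyses section states intention to treat.

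**The concern.** A sample size formula returns the number of patients who must contribute an outcome. Here that number is printed as the maximum to recruit. The two figures agree only if nobody is lost between allocation and the 6-week assessment, and the protocol itself names two ways in which a patient can be lost. A consented and allocated patient can withdraw. A patient randomised before surgery can have the operation cancelled, and then no postoperative outcome exists.

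What is at stake is how a non-significant complication result is read. A reader would take it to come from a comparison with 80% power for a fall from 30% to 10%, when the planned maximum gives somewhat less once any outcomes are missing.

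**Working it through.** **Inputs.** Control 30%, intervention 10%, at 6 weeks; power 80%; type 1 error 5% (all from Sample size). Allocation is 1:1 (Randomisation section: "stratified by centre with a 1:1 allocation using random block sizes"). The test is taken as two-sided. The article does not say so, but a two-sided test reproduces the printed figure, and the same formula one-sided gives 46.4, so 47.

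**Reproducing the plan's figure.** Unpooled two-proportion formula, no loss:

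n per group = (z₀.₉₇₅ + z₀.₈₀)² × [p₁(1−p₁) + p₂(1−p₂)] / (p₁−p₂)²

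= (1.960 + 0.8416)² × (0.21 + 0.09) / 0.20²

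= 7.849 × 0.30 / 0.04 = 58.87, rounded up to 59.

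The arcsine formula gives 59.01. The printed 59 is therefore the number to be analysed, with nothing added. The pooled-variance formula would give 62, and the continuity-corrected formula 72.

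**Power with complete data.** Enumerating all binomial outcomes at 30% v 10% and applying the uncorrected Pearson chi-square test at two-sided 5% gives 80.5% at 59 per group. At 58 per group it is 79.7%, so losing one patient per group already takes the figure just below 80%.

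**Power after loss.** The documents give no loss rate. The percentages below are assumptions, applied equally to both groups and rounded to whole patients, for example 59 × 0.90 = 53.1, so 53.

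| Assumed loss by 6 weeks | Per group with outcome | Exact chi-square power | Unpooled normal approximation |
|---|---|---|---|
| 0% | 59 | 80.5% | 80.1% |
| 5% | 56 | 78.1% | 78.0% |
| 10% | 53 | 75.5% | 75.8% |
| 15% | 50 | 73.4% | 73.3% |
| 20% | 47 | 70.5% | 70.7% |

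The Statistical analyses section also names Fisher's exact test. With that test, power is 72.0% at 59 per group with no loss and 69.4% at 56. The table therefore uses the more favourable of the two named tests.

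**Can loss follow allocation?** Withdrawal can, because the envelope is opened after consent and consent can be withdrawn at any time. Cancellation can, for patients who consent and are randomised before surgery. It cannot for those who consent after the operation. The article does not say how many patients fall in each group.

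**The case against.** The strongest reply is that 59 is arithmetically right and that a condensed article may leave attrition to the full protocol. The first half stands: there is no calculation error. The second half would stand if the point were only a missing dropout paragraph. But the article prints a recruitment maximum, a power and an exclusion list that do not allow for one another, and that can be judged from the printed text.

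It can also be said that the maximum is not a hard ceiling. The section gives a minimum of 2×12 for abstinence and a maximum of 2×59 for complications, so the words may only mark the smaller and the larger requirement. About 20 patients at each of the six initial centres would be 120. That reading is possible, but 120 against 118 is no real margin, and the sentence still speaks of patients to be recruited.

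Several limits stand in full:

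- The exclusion list does not separate events before and after allocation, and it does not say that randomised patients are dropped from the analysis. How it fits with intention to treat is a separate question.
- Record follow-up with permission can recover some complication outcomes, since complications requiring treatment should largely appear in records. It cannot help for patients who refuse, or where no operation took place.
- The powered time point is 6 weeks. Missed visits at 3 to 12 months do not affect the stated power.
- At 5% loss the shortfall is about 2 points, no larger than the gap between the pooled (78.2%) and unpooled (80.1%) approximations at 59 per group with no loss.

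A reader might infer that the plan cannot deliver 80% power, or that it certainly removes randomised patients. The documents support neither: complete 6-week data would give 80.5%, and no loss rate is stated.

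**Conclusion.** The point holds in a limited form. The number 59 per group is correct as the number with a 6-week complication outcome, but it is stated as the most to be recruited, with no margin. Because consent withdrawal and cancelled surgery can both follow allocation, the stated 80% applies only if essentially every randomised patient has that outcome.

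Under assumed losses of 5% to 20%, power falls to about 78% to 70.5%. This rests on the planning rates of 30% v 10%, a two-sided 5% uncorrected chi-square test, equal loss in both groups, and loss counted after any recovery from records. The size of the shortfall depends on the assumed loss. That the figure has no margin does not.

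**What to change.** Reword the sample size sentence to say that 80% power requires 59 patients per group with a 6-week complication outcome, and that recruiting at most 2×59 gives about 70% to 78% power for 20% to 5% loss by 6 weeks. Say that these powers are for the planning rates of 30% v 10%. They should not be recalculated from the observed rates, and a non-significant result is better read through its confidence interval.

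No extra enrolment is asked for, and the Project status section reports that inclusion is already closed. The cost is one sentence and a slightly less favourable stated power.
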